## Abstract

**Background:**

Preterm birth (PTB) is a leading cause of infant morbidity and mortality worldwide. Every year, 20 million babies are born with low birthweight (LBW), about 96% of which occur in low-income countries. Despite the associated dangers, in about 40%-50% of PTB and LBW cases, the causes remain unexplained. Existing evidence is inconclusive as to whether occupational physical activities such as heavy lifting are implicated. African women bear the transport burden of accessing basic needs for their families. Ghana’s PTB rate is 14.5%, whereas the global average is 9.6%. The proposed liftless intervention aims to decrease lifting exposure during pregnancy among Ghanaian women. We hypothesize that a reduction in heavy lifting among pregnant women in Ghana will increase gestational age and birthweight.

**Objective:**

To investigate the effects of the liftless intervention on the incidence of PTB and LBW among pregnant Ghanaian women.

**Methods:**

A cohort stepped-wedge cluster randomized controlled trial in 10 antenatal clinics will be carried out in Ghana. A total of 1000 pregnant participants will be recruited for a 60-week period. To be eligible, the participant should have a singleton pregnancy between 12 and 16 weeks gestation, be attending any of the 10 antenatal clinics, and be exposed to heavy lifting. All participants will receive standard antenatal care within the control phase; by random allocation, two clusters will transit into the intervention phase. The midwife-led 3-component liftless intervention consists of health education, a take-home reminder card mimicking the colors of a traffic light, and a shopping voucher. The primary outcome are gestational ages of <28, 28-32, and 33-37 weeks. The secondary outcomes are LBW (preterm LBW, term but LBW, and postterm), compliance, prevalence of low back and pelvic pain, and premature uterine contractions. Study midwives and participants will not be blinded to the treatment allocation.

**Results:**

Permission to conduct the study at all 10 antenatal clinics has been granted by the Ghana Health Service. Application for funding to begin the trial is ongoing. Findings from the main trial are expected to be published by the end of 2019.

**Conclusions:**

To the best of our knowledge, there has been no randomized trial of this nature in Ghana. Minimizing heavy lifting among pregnant African women can reduce the soaring rates of PTB and LBW. The findings will increase the knowledge of the prevention of PTB and LBW worldwide.

**Trial Registration:**

Pan African Clinical Trial Register (PACTR201602001301205); http://apps.who.int/trialsearch/ Trial2.aspx?TrialID=PACTR201602001301205 (Archived by WebCite at http://www.webcitation.org/71TCYkHzu)

**Registered Report Identifier:**

RR1-10.2196/10095

## Introduction

Preterm birth (PTB) and low birthweight (LBW) are increasing worldwide, especially within low-and middle-income countries (LMIC). Every year, 15 million babies are born before 37 completed weeks [1,2] and 20 million (15.5%) babies are born with LBW (˂2500 g) worldwide. Approximately 96% of these births occur in LMIC [1]. It is estimated that LBW infants are at a 20-fold greater risk of neonatal mortality than babies with a birthweight of 3.5-4.0 kg. Approximately 28% of neonatal deaths (first 7 days of life) are a result of PTB [3]. PTB is a major contributing factor to LBW [1]. Millions of preterm and LBW babies die as a result of preventable complications, and some of those who survive will live with lifelong debilitating health conditions [1,4,5]. PTB is a problem even in high-income countries (HIC). The rate of PTB in the United States increased from 9.5% in 1981 to 12.7% in 2005 [6]. The rate of PTB averages 9.6% worldwide and varies between Europe (6.2%) and North America (10.6%) [6]. In LMIC, the incidence of LBW is around 19%, compared with 5%-7% in HIC [7]. Southern Asia and sub-Saharan Africa have recorded 60% of global PTBs in 2010; Ghana was ranked 14th of 184 countries, with a PTB rate of 14.5% in 2010 [2].

There is widespread agreement on the need for immediate action to prevent PTB and LBW. However, this cannot be completed without a critical look at the occupational environment of the ever-increasing global female workforce [8]. A greater number of women in LMIC work in the informal sector [9], and their work entails repetitive lifting and carrying [10] with virtually no ergonomic guidelines to safeguard their welfare. Evidence suggests that most African women perform an average of 328 trunk flexions at angles exceeding 60º in an 8-hour period each day. Of these trunk flexions, 66 are sustained for >4 seconds [11]. In household settings, African women bear most of the transport burden of accessing basic needs such as water, farm produce, and firewood. The average African woman carries a load of about 20 kg over a distance between 2.5 and 6.8 km on a daily basis [11]. The physical stress encountered by these women can result in musculoskeletal disorders and negative reproductive consequences [12-14]. The activities of ordinary Ghanaian women in rural and periurban areas include farming, carrying water and farm produce on their heads, carrying market wares during street hawking, and carrying their younger children on their backs (at home, to the market, and to the farm).

Some observational studies have implicated occupational lifting or heavy physical workload during pregnancy in the causal pathways of PTB and LBW [1,12,15-17], although others did not reach clear conclusions [18]. However, exposure may have been poorly measured, thereby distorting the outcome of such studies. The Occupational Health Clinic for Ontario Workers reported that a 4.5 kg weight carried further away from the back during pregnancy exerts 68 kg of stress on the lower back, compared with 29.5 kg of stress in a nonpregnant woman [19]. A rise in intra-abdominal pressure resulting from lifting can initiate premature uterine contractions [10], and lifting increases the risk of pelvic pain during gestation [20].

There have been many successful health education and advice-oriented interventions that have improved patient outcomes [21]. In their quest to lengthen gestational age, midwives in LMIC such as Ghana advise pregnant women against strenuous physical activity. In certain conditions, the pregnant woman is admitted to a hospital throughout the gestational period to ensure complete bed rest to avert possible PTB [22]. Several occupational guidelines have been formulated by various institutions [19,23] aimed at protecting pregnant employees against physical stress in their respective countries. More recent are the provisional clinical guidelines for occupational lifting in pregnancy by MacDonald et al [24]. However, no such guidelines exist in Ghana and other LMIC. A recent systematic review revealed that no trial has investigated the usefulness of such guidelines aimed at reducing heavy lifting among pregnant women to increase gestational age [22]. The 3-component liftless intervention implemented in this trial is based on the clinical guidelines of occupational lifting in pregnancy by MacDonald et al [24] coupled with a shopping voucher. The rationale for the shopping voucher is to augment the uptake of the intervention components [25,26]. The shopping voucher will be administered during the third trimester with the intention of reducing moderate PTB, which is common in sub-Saharan Africa [2]. As no randomized controlled trial (RCT) has been conducted to ascertain the effectiveness of the proposed liftless intervention, the outcomes will be of public health importance for elucidating the effects of heavy lifting on birth outcomes (PTB and LBW). Through this study, a model for intervention to reduce physical exertion during pregnancy will be developed and its impact on reducing PTB and LBW will be ascertained. The success of the proposed stepped-wedge trial will justify the need for clinical guidelines to modify the occupational and family environment of pregnant women in LMIC. We hypothesize that a reduction in heavy lifting among pregnant women in Ghana will increase gestational age and birthweight.

The objective of this study is to investigate the effects of the liftless intervention on the incidence of PTB and LBW among pregnant Ghanaian women. This study aims (1) to provide guideline-oriented and social support (liftless intervention) to Ghanaian women to reduce their lifting behavior during pregnancy; (2) to evaluate the effect of the liftless intervention on rates of PTB, LBW, mode of delivery, lower back or pelvic pain, and premature uterine contractions compared to no such intervention; and (3) to examine compliance with the intervention and ascertain factors that influence it.

## Methods

### Study Design

We propose an open cohort stepped-wedge cluster RCT (PACTR201602001301205). In this design, eligible participants will be recruited until the expected numbers have been achieved. The design is a unidirectional cross-over study wherein all participating antenatal clinics will start with a control phase and eventually end up providing the intervention. The intervention will not be withdrawn once implementation has begun (at least not until the end of the trial). Participants will leave the trial when they deliver. Baseline measurements and information will be collected in all 10 clusters at the beginning of the trial using a 55-item data collection tool. Using random allocation, two clusters will transition into the intervention with each phase lasting 10 weeks. With the exception of clusters 1 and 2 (Figure 1) [27], the rest of the clusters will contribute data to the control more than once. Clusters 9 and 10 will contribute control data at 5 time points before the intervention is implemented. Thus, unlike a traditional cluster RCT where the intervention is administered only to those in the treatment group, every cluster in the stepped-wedge RCT will receive the intervention. The flow of the trial is shown in Figure 2 [28].

During the control phases, participants will receive routine antenatal care including physical and abdominal examination, blood pressure and weight measurement, urine testing, prescription of iron and folic acid supplementation, and tetanus injection. When a clinic enters the intervention phase, in addition to receiving routine antenatal care, participants will attend 5 extra intervention sessions at weekly intervals. During the sessions, study midwives will deliver the 3-component liftless intervention explaining and demonstrating all of the potential harmful task conditions, providing a take-home reminder card, and soliciting for a partner’s support. In addition, midwives will make phone calls, do home visits, and provide the shopping vouchers.

The choice of the stepped-wedge design for this trial is based on the anticipation that the intervention will be useful. This design allows the intervention to be offered to all clusters, reduces potential contamination of the control group [29], and provides an opportunity to gradually roll out the intervention to resolve any financial or logistical constraints that may arise at the clinics concurrently. To ensure completeness of the protocol, the Standard Protocol Item: Recommendations for International Trials 2013 recommendation was followed [28].

### Study Population and Recruitment

The trial will be conducted at 10 public antenatal clinics in Ghana (the lists of clinics are provided in Multimedia Appendix 1). Eligible clinics will be those that offer antenatal services. The selected clinics are located in 4 cities in Ghana. The clinics will recruit 1000 participants within a period of 60 weeks. Although the facilities vary in size, they are located in areas that have sufficient numbers of pregnant women to make the trial feasible. The socially ascribed activities of most women within the catchment areas of the proposed antenatal clinics include carrying water and farm produce on their heads as well as carrying market wares as street vendors. Most women also carry their younger children on their backs at home, to the market, and to the farm. Additional antenatal clinics will be added to meet the planned target if necessary. The study midwives will recruit participants based on the prespecified participant-level criteria (Textboxes 1 and 2). The nature of the trial and the required commitment on the part of participants will be explained to the participants by the research midwives in a language that they understand. Participation is voluntary and decisions will not affect the routine antenatal care they will receive. Those who agree to participate and are eligible will be provided with a consent form to sign or thumb print (the copy of consent form is available on request from the authors).

### Outcomes

#### Primary outcome

The primary outcome is gestational age based on ultrasound examination in the first trimester (before 16 weeks), or when not available, fundal height and last menstrual period. We expect that only about 10% of the pregnancies will be without ultrasound diagnosis. We will still include these to prevent increasing the workload of the recruiting midwives. We will conduct a sensitivity analysis to see if there is an effect of the ultrasound versus last menstrual period and fundal height diagnosis. We will categorize PTB as extremely preterm (<28 weeks), very preterm (28-32 weeks), or moderate to late preterm (33-37 weeks) based on the World Health Organization classification [30].

#### Secondary outcomes

The secondary outcomes are as follows:

Birthweight categorized as preterm LBW, full term but LBW, or postterm LBW babies [7].Compliance with the intervention (classified as compliant or noncompliant). We will classify a participant as compliant (1) if the weight and frequency of lifting have decreased to below the provisional guidelines and (2) if lifting below or above the knee or shoulders has decreased, based on the participant’s self-reported lifting and observations during home and workplace visits.Prevalence of lower back pain or pelvic pain: yes or no; frequency: sometimes or most of the time; stage of pregnancy: first or second or third trimester; severity: mild or moderate (interferes with daily function or severe and needs analgesics to subside).Premature uterine contractions: yes or no; frequency: sometimes or most of the time; stage of pregnancy: first or second or third trimester.Mode of delivery: normal or forceps or cesarean section, as recorded on birth and postnatal records.

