### Statistical Analysis and Sample Size

We will compare the average proportion of all outcomes in the intervention group clusters to the control group clusters. We will test our hypothesis using a logistic regression model with a random effect for cluster and a fixed effect for each step of implementation of the intervention to adjust for possible effects of calendar time [34,35].

If there are major baseline differences between the intervention and control clusters for potential confounders, such as prolonged standing or squatting, parity, maternal age, infection, occupation, educational level, marital status, and nutritional status, we will include these as covariates in the model. Intention to treat will be the basis for the statistical analysis to ensure that all clusters (with participants) are randomized and included in the final analysis regardless of completion of the study or not [36].

For the sample size calculation, we set alpha at 0.1 and beta at 0.8. We assumed that the intervention will decrease PTB rate by 30% (ie, from 14.5% to 10.5%, with 14.5% being the current official PTB rate in Ghana). With 10 antenatal clinics, we estimated that we need 1000 participants to provide the power to detect a 30% difference in the rate of PTB between the control and intervention clusters. The individual performing the analysis will be blinded to the treatment allocation.

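### The birthweight outcome is defined only as LBW split by gestational age at birth, so neither the overall LBW rate nor higher birthweight is defined as an endpoint, and term LBW read alone could rise despite benefit

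*Protocol article*

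**What the plan says.** All references are to the protocol article.

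- **Objective (end of the Introduction):** to study "the effects of the liftless intervention on the incidence of PTB and LBW among pregnant Ghanaian women". The second aim is "to evaluate the effect of the liftless intervention on rates of PTB, LBW, mode of delivery, lower back or pelvic pain", with LBW not split by gestation.
- **Hypothesis (Introduction):** less heavy lifting "will increase gestational age and birthweight".
- **Secondary outcomes:** "Birthweight categorized as preterm LBW, full term but LBW, or postterm LBW babies". This list contains no pooled LBW yes/no outcome, no birthweight in grams and no category for babies of 2500 g or more.
- **Abstract, Methods:** "The secondary outcomes are LBW (preterm LBW, term but LBW, and postterm), compliance". The third category here lacks the LBW qualifier that it has in the Secondary outcomes section.
- **Statistical Analysis and Sample Size:** "We will compare the average proportion of all outcomes in the intervention group clusters to the control group clusters", using a logistic model with clinic as a random effect and step as a fixed effect.
- **Primary outcome:** gestational age, with preterm birth in three bands.
- **Introduction and Data Collection Tools:** LBW is a weight below 2500 g, and birthweight and gestational age are both read from the antenatal and postnatal cards.

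**The concern.** The outcome definition does not line up with the question. The objective needs one LBW rate and the hypothesis needs a measure of weight, but the definition gives three subsets of LBW.

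The subsets are formed by a variable that the intervention is meant to change. Two things follow if each category is compared between control and intervention periods. Preterm LBW falls whenever preterm birth falls, even if weight for a given gestation is untouched. And a baby that would have been born preterm and LBW, but is now born at term and still under 2500 g, leaves one category and enters another. Term LBW can then look worse because the intervention worked.

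At stake is the interpretation of the LBW half of the objective. The primary preterm birth result is not affected.

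**Working it through.** The article gives no LBW rate, so there is no LBW figure of its own to reproduce. The check is an accounting exercise.

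**Inputs from the article.** Preterm birth 14.5% in control and 10.5% under intervention (Statistical Analysis and Sample Size), so 4.0 points are averted and 85.5% of control births are not preterm. LBW is under 2500 g (Introduction).

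**Assumptions, not in the article.**
- p, the share of preterm babies who are LBW: 0.60 (range 0.50 to 0.70)
- t, the share of other babies who are LBW: 0.05 (range 0.04 to 0.06)
- s, the share of LBW babies moved to term who stay under 2500 g: 0.50 (range 0.30 to 0.70)
- m, the relative fall in LBW among births that would be term anyway: 0 unless stated

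Postterm births are counted with term births.

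**Formulas, in % of all births.**
- Preterm LBW: 14.5 × p in control; 10.5 × p under intervention
- Term LBW: 85.5 × t in control; 85.5 × t × (1 − m) + 4.0 × p × s under intervention

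**Control, central values.** Preterm LBW 14.5 × 0.60 = 8.7. Term LBW 85.5 × 0.05 = 4.275. Total 12.975.

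**Intervention, central values.** Preterm LBW 10.5 × 0.60 = 6.3. For term LBW:

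| s | m | Term LBW | Change in term LBW | Total LBW |
|---|---|---|---|---|
| 0.50 | 0 | 4.275 + 1.2 = 5.475 | +1.20 | 11.775 |
| 0.50 | 0.10 | 3.8475 + 1.2 = 5.0475 | +0.77 | 11.3475 |
| 0.50 | 0.30 | 2.9925 + 1.2 = 4.1925 | −0.08 | 10.4925 |
| 0 | 0 | 4.275 | 0 | 10.575 |

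**Results.**
1. With m = 0 the central case is a relative rise in term LBW of 1.2 / 4.275 = 28%, while total LBW falls by 1.2 points.
2. Over the assumed ranges with m = 0, the relative rise runs from 0.6 / 5.13 = 12% to 1.96 / 3.42 = 57%. Total LBW changes by −4.0 × p × (1 − s), which is −0.6 to −1.96 points, so it falls throughout.
3. The rise vanishes when 85.5 × t × m equals 4.0 × p × s. In the central case that is m = 1.2 / 4.275 = 0.28.
4. With p constant, the relative fall in preterm LBW is 2.4 / 8.7 = 27.6%, the same as that in preterm birth, 4.0 / 14.5 = 27.6%. On these inputs the category adds nothing to the primary result.
5. Precision: assume 500 women per condition and ignore clustering. The standard error of 5.475% minus 4.275% is √(0.04275 × 0.95725 / 500 + 0.05475 × 0.94525 / 500) = 0.0136, or 1.36 points, so z = 1.20 / 1.36 = 0.88.
6. Denominator: the definition lists LBW babies only. If proportions were taken among LBW babies, then even with s = 0 and m = 0 the term share would go from 4.275 / 12.975 = 33% to 4.275 / 10.575 = 40%, purely because preterm births were prevented.

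**The case against.** A reader might infer that nothing in the trial measures total LBW, so that the LBW question cannot be answered. The article does not support that. The Abstract names LBW as a secondary outcome, the second aim names its rate, the 2500 g cut-off is given, and the three categories in the Secondary outcomes section do not overlap and add up to all LBW. What stands is narrower: the section that defines the outcomes does not define the pooled endpoint, and birthweight as a measurement is not an endpoint anywhere.

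A reader might also infer that a real benefit would show as a rise in term LBW. That is not established. The rise requires that some averted preterm births stay under 2500 g and that weight at term improves little, whereas the hypothesis expects birthweight to rise. With enough improvement at term, the category is flat or falls. Any rise is also small against its precision (z about 0.9 before clustering), and a larger fall in preterm LBW would be reported beside it.

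Two further points are fair. The analysis section speaks of proportions of all outcomes. It does not state a separate test for each category, and an analysis plan not shown here may settle that. The split itself is a cited classification and helps to separate LBW due to early birth from LBW due to poor growth. Both argue for keeping the split as a breakdown. Neither supplies the endpoint that the objective and hypothesis call for.

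**Conclusion.** The point holds as a mismatch between the stated outcome and the stated question. The Secondary outcomes section fixes birthweight only as LBW divided by the primary outcome; overall LBW is derivable but not defined, and birthweight in grams is absent although the hypothesis is about it. Preterm LBW partly repeats the primary result. Term LBW read alone could mislead: 4.3% to 5.5% in the central illustration, 12% to 57% in relative terms over the assumed ranges, with no rise once LBW among births that would be term anyway falls by about 28% in the central case. All LBW shares are assumptions; only the two preterm birth rates and the 2500 g cut-off come from the article.

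The outcome is secondary, and design, recruitment and the primary analysis are untouched. This should be fixed, but the trial does not depend on it.

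**What to change.** In the Secondary outcomes section, define:

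1. LBW as birthweight under 2500 g at any gestational age, with all births as the denominator, analysed in the planned mixed logistic model.
2. Birthweight in grams, analysed in the matching linear mixed model with the same clinic and step terms.

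Report preterm, term and postterm LBW as a descriptive breakdown, with a note that the categories depend on the primary outcome. Reconcile the third category in the Abstract (*postterm*) with that in the Secondary outcomes section (*postterm LBW*).

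The cost is a change of wording and one extra model. Birthweight is already read from the cards, so no new measurement is needed.

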**Figure 2 figure2:**
[figure not shown]
Flow of the trial (adopted from Standard Protocol Item: Recommendations for International Trials 2013).

Inclusion criteria.Inclusion criteria1. Pregnancy has been clinically confirmed.2. Pregnancy is between 12 and 16 weeks.3. Pregnancy is singleton.4. Exposed to lifting of 10 kg at home or work.5. Attending 1 of 10 antenatal clinics.6. Participant has consented to participate in the trial.

Exclusion criteria.Exclusion criteria1. Pregnancy has not been confirmed.2. Gestational age is above 16 weeks.3. Multiple pregnancies.4. Not exposed to lifting.5. Not attending any of the selected clinics.6. Refusal to participate.

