##### STOP (Yellow)

Lifting heavy loads that weigh >10 kg, either at home or at work.Lifting more than once per 5 minutes after pregnancy has been confirmed until term.Lifting or lowering objects below the knee.Lifting items over shoulder height.

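### Compliance condition (2) scores only a decrease in low or high lifting, so a woman who never does it is classed noncompliant and baseline lifting pattern leaks into aim 3

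*Protocol article*

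**What the plan says.** Under Secondary outcomes, the protocol article lists "Compliance with the intervention (classified as compliant or noncompliant") and gives two conditions joined by the word *and*. Condition (1) is met "if the weight and frequency of lifting have decreased to below the provisional guidelines". Condition (2) is met "if lifting below or above the knee or shoulders has decreased". Both are to be judged "based on the participant’s self-reported lifting and observations during home and workplace visits".

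The behaviour taught is an absolute target. Component 1 (Health Education) includes avoiding lifts over shoulder height and avoiding lifting or lowering below the knee. The STOP (Yellow) part of the reminder card repeats both, for example "Lifting or lowering objects below the knee".

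The lifting exposure required for entry is "Exposed to lifting of 10 kg at home or work". The inclusion criteria say nothing about lift height. Low and high lifting are recorded at baseline in the 55-item questionnaire (Data Collection Tools and Data Management).

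The third of the three aims in the Introduction is "to examine compliance with the intervention and ascertain factors that influence it".

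**The concern.** The rule scores a change, while the trial teaches a level. Where the two come apart, the classification is wrong in both directions: a woman who fully follows the advice on lift height can fail, and a woman who largely ignores it can pass.

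What is at stake is the third aim. When part of an outcome is defined by a fall from baseline, the baseline value predicts the outcome by construction. A factor associated with how women lifted before the trial, such as occupation, could then appear to influence compliance although it made no difference to how well the advice was followed.

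This is not a detail left for an analysis plan to fill in. The article states the classification rule, and applying that rule as stated produces the error.

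**Working it through.** There is no figure in the article to reproduce. The check applies the written rule to the women who can be enrolled and compares the result with the behaviour taught.

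**Step 1. Can women with no low or high lifting at baseline enter?** Yes. Entry needs exposure to lifting of 10 kg and sets no requirement on lift height.

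**Step 2. Apply condition (2).** The daily counts are illustrative and cover lifts below the knee or above the shoulder.

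| Baseline | Follow-up | Does what the card asks on lift height? | Has decreased, so condition (2) met? |
|---|---|---|---|
| 0 | 0 | Yes | No |
| 20 | 0 | Yes | Yes |
| 20 | 19 | No | Yes |
| 0 | some | No | No |

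The first and third rows are misclassified on this condition.

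**Step 3. Carry this through to the full definition.** Both conditions are required, so the woman in the first row is noncompliant whatever she does about weight and frequency. The woman in the third row is compliant overall only if she also meets condition (1). That is possible. Taking the card's limits as those of the guideline (an assumption, since the article does not set out the guideline in full), one lift per 5 minutes is 60 / 5 = 12 an hour. Nineteen lighter, spaced lifts in a day fit within that.

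**Step 4. Ceiling on observable compliance.** Let q be the share of women with no low or high lifting at baseline. The article does not give q; the values below are assumptions. With perfect behaviour by every woman, the highest compliance the rule can record is 1 − q:

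- q = 5%: 1 − 0.05 = 95%
- q = 10%: 1 − 0.10 = 90%
- q = 20%: 1 − 0.20 = 80%
- q = 40%: 1 − 0.40 = 60%

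**Step 5. Effect on aim 3.** Suppose two occupational groups follow the advice equally and perfectly, but q is 5% in one and 20% in the other (assumed). The rule records 95% and 80%, a difference of 95 − 80 = 15 percentage points that reflects baseline lifting pattern alone.

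**Step 6. Alternative reading.** If either condition were enough, women starting at none could qualify through condition (1). One fewer low lift would then make any woman compliant outright, so the definition would still be faulty.

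**The case against.** The strongest reply is that few women will be affected. Study Population and Recruitment describes most women in the catchment areas as head-loading water and farm produce, and putting a load on the head would normally mean lifting above the shoulder. The Introduction cites an average of 328 deep trunk flexions per 8 hours among African women. This stands as a caution on size: it does not show that q is zero, but it argues against assuming a large q. It does not rescue the rule, because women who do have such lifting at baseline are open to the opposite error, where a token decrease is enough.

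A second reply is that scoring a woman at none is an operational detail that a condensed article may leave out. That would be fair if the article were silent. It instead states a rule under which she fails.

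Several stronger readings are tempting, and the article does not support them:

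- *Condition (1) has the same fault.* It names a threshold, so its natural reading is a level. On weight, entry at 10 kg against a card limit of more than 10 kg means that few women start clearly below the limit. A doubt remains for frequency, since entry sets no minimum.
- *Condition (2) also covers lifts between knee and shoulder.* The grammar is compressed, but Data Collection Tools and Data Management states the same variable plainly as below the knee or above the shoulders.
- *A trivial decrease makes a woman compliant.* It satisfies condition (2) only; condition (1) must also be met.
- *The preterm birth result would be distorted.* No compliance-based analysis of preterm birth is described, and Statistical Analysis and Sample Size makes intention to treat the basis.

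**Conclusion.** The definition is faulty as stated. Condition (2) rewards a fall from baseline where the intervention teaches avoidance, so women with no low or high lifting throughout are noncompliant by construction and any small decrease meets the condition. The consequence is confined to the compliance outcome and the third aim; the primary outcome and the sample size are untouched.

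The number misclassified cannot be determined from the article and may be small. The ceilings above illustrate how the rule behaves and do not estimate the bias; a reader should not infer any particular loss in the compliance rate from them. The conclusion that women starting at none cannot be compliant rests on both conditions being required. The conclusion that the definition is faulty does not.

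**What to change.** Reword the one outcome definition:

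- Score condition (2) by status at follow-up against the trial's own reminder card, so that a woman with no lifting below the knee or above the shoulder at follow-up meets it whatever her baseline.
- State that condition (1) means being within the guideline on weight and frequency at follow-up, which removes the doubt about women already within the frequency limit.
- Report change from baseline in low and high lifting as a separate measure, so that partial reductions are not lost.
- Keep the sources the definition already names: self-report and the home and workplace observations.

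No new lifting limit is needed. There are two modest costs. Lift height is named only for the questionnaire, while the diary is described as recording frequency and weight, so the diary or the visit checklist may need one added item. A strict level will also give a lower compliance rate among women who reduce such lifting without stopping it, which is why change should be reported alongside.
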